### Patient recruitment

Recruitment commenced in September 2021 and will continue until the sample size is reached. Recruitment is expected to be completed at the end of 2023.

Participants are recruited from all over Denmark and are primarily referred from regional headache clinics and the Danish Headache Center, a tertiary headache referral center.

## Methods: assignment of interventions

### Randomization and blinding

After the 14-day grace period following ONS implantation, the ONS systems will be programmed and the participants will be allocated 1:1 in the two study groups (burst ONS or placebo). The allocation is conducted by block randomization with blocks of random size between four and eight, using a specially designed automated electronic randomization tool. The allocation tables for the randomization are inaccessible to the investigators and other staff involved in the project.

The randomization is performed by the implanter or the project nurse who is responsible for the programming of the ONS systems. These personnel are unblinded throughout the entire trial and are therefore able to handle any ONS-related events during the blinded trial phase without mitigating the blinding. Unblinded personnel will not have any role in data collection, management, and analysis.

The participants are blinded to their allocation group. The principal investigator and other study personnel who perform the evaluation of outcome parameters, are blinded to the allocation group as well, and will not have access to the randomization tool in the project database. Blinding is maintained until all participants have completed the final trial phase.

The IPGs used in the study are non-rechargeable units to ensure that a lack of need for recharging does not unblind the participants. In addition to this, to avoid accidental unblinding, the participants will not have the remote controls to the ONS system during the blinded trial phase, since the display would reveal if stimulation is on. Importantly, when treated with burst stimulation, participants should not have any sensation of stimulation and, hence will not need to adjust the stimulation amplitude. The postoperative 14-day grace period ensures accurate programming, which in our experience limits the need for stimulation adjustments within the 12 weeks of blinded trial to an absolute minimum. If needed, patients can directly contact the principal investigator. Should the participants get a sensation of stimulation during the blinded trial phase, unblinded personnel can adjust the stimulation settings if necessary.

When crossing over to the open-label tonic ONS trial phase, all participants are equipped with a remote control.

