## Methods: Participants, interventions, and outcomes

### Study design

The study is an investigator-initiated, prospective, double-blinded, randomized, placebo-controlled trial.

After an initial baseline period, all participants are treated with TENS. Following the TENS trial all participants are implanted with an ONS system and randomized into one of two arms; one intervention arm and one placebo arm with an allocation ratio of 1:1. The participants in the intervention arm receive burst ONS (paresthesia-free stimulation). In the placebo group, the ONS system will be left turned off. In the final trial phase, all participants cross over to open-label tonic ONS (Fig. 1).

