**Primary endpoints:**
1. 30% reduction in attack frequency with TENS and ONS
2. Safety in ONS and TENS treatment

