### Statistical analysis

Statistical analysis will be conducted by the principal investigator and a statistician blinded for treatment allocation only after follow-up for all participants is completed. No interim analysis will be performed.

Characteristics of the patients will be presented using descriptive statistics to assess if balanced groups were obtained after randomization. The primary analysis will be conducted according to the intention-to-treat principle to avoid introducing bias. In a secondary analysis, a per-protocol analysis will be performed.

The primary outcome is a 30% reduction in attack frequency with TENS and ONS treatment compared to baseline. Relative change in attack frequency (in percent) will be analyzed using the Wilcoxon signed-rank test for paired variables, comparing the baseline data with data from the TENS trial and the trial with burst and tonic ONS, respectively. Because the changes in attack frequency are expectedly skewed [23], a non-parametric test will be applied. In cases with a minimum 30% reduction in attack frequency, sub-analyses will be made to group the treatment responders after relevant cutoffs.

Analysis of the secondary outcomes will be conducted according to the same principle, comparing data from each of the trial phases to baseline using a parametric or non-parametric test for paired variables, depending on the data distribution.

The feasibility of TENS as a predictor for ONS outcome will be evaluated by determining the sensitivity and specificity and calculating the predictive values.

Statistical data analysis will be performed using Stata 17.0 (StataCorp, College Station, USA-TX).

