### Adverse events

The principal investigator is responsible for continuously registering adverse events and side effects of any kind related to the TENS and ONS treatment. Data on all adverse events and side effects are registered and logged in the project-specific REDCap database. All side effects and adverse events are reported to the Central Denmark Region Committee on Health Research Ethics once a year, and collectively when the project is completed. Serious adverse events will be reported immediately to the Central Denmark Region Committee on Health Research Ethics.

In the blinded trial phase (burst ONS vs. placebo), none of the participants have access to the remote control for their ONS system, as this could potentially reveal the randomization of the participant. A clinical control after the postoperative grace period of 14 days is scheduled to ensure optimal conditions for program optimization. Should the participants suspect a problem related to the ONS system, direct contact can be made with the principal investigator, and the participant will then be seen by project staff who are trained in programming the system and who are unblinded for the randomization group. Where necessary, a clinical evaluation will be made by the ONS implanters at the Department of Neurosurgery, Aarhus University Hospital.

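### In the blinded phase, participants who suspect a device problem can go first to the blinded principal investigator, who may thereby learn the likely allocation while registering adverse events and sharing the analysis

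*Protocol article*

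**What the plan says.** The Randomization and blinding section sets the investigator's status: "The principal investigator and other study personnel who perform the evaluation of outcome parameters, are blinded to the allocation group as well". It gives the handling of ONS-related events in the blinded phase to the implanter and project nurse, who know the allocation, and keeps those persons out of collecting, managing and analysing data. The blind is to last until the last participant has finished the tonic phase.

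The same section offers participants a contact: "If needed, patients can directly contact the principal investigator". The sentence before it concerns stimulation adjustments. The sentence after it reads: "Should the participants get a sensation of stimulation during the blinded trial phase, unblinded personnel can adjust the stimulation settings if necessary".

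The Adverse events section gives the order of events for a suspected device problem: "direct contact can be made with the principal investigator, and the participant will then be seen by project staff". Those staff are described there as unblinded.

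The investigator has two further tasks. Under Adverse events: "The principal investigator is responsible for continuously registering adverse events and side effects of any kind". Under Statistical analysis: "Statistical analysis will be conducted by the principal investigator and a statistician blinded for treatment allocation". The second primary endpoint in Table 4 is "Safety in ONS and TENS treatment".

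**The concern.** A report made by a participant can carry information about the arm. The Study design section states: "In the placebo group, the ONS system will be left turned off". A true sensation of stimulation in this phase can therefore come only from an active burst device. Where such a report goes first to the investigator, a blinded person may learn a participant's likely allocation without any access to the randomization module.

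At stake is the independence of the safety record and of the analysis. The investigator registers events related to treatment, and doing so while believing a participant is on burst can influence what is recorded and what is attributed to the device. Some analysis decisions are also still open in the article: the responder cutoffs are not named, the choice between parametric and non-parametric tests depends on the data, and a per-protocol analysis is planned.

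**Working it through.** No figure in the plan bears on this point, so the check sets the sections side by side.

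1. **Who should handle device events.** Randomization and blinding: the unblinded implanter and nurse, so that the blind is protected.
2. **Whom the participant can contact first.** Randomization and blinding (in general terms) and Adverse events (for a suspected ONS problem): the blinded principal investigator. Unblinded staff come second.
3. **What the contact may convey.** Burst is set at 50% of the detection threshold (Burst ONS section) and should not be felt, but the protocol foresees that it sometimes may be. Placebo is off. Participants know the feeling from transcutaneous stimulation (TENS) and from the on-table test at implantation, so they can describe it. A described sensation points to burst. A report of pain at the generator site or a suspected lead fault does not, since either arm can have these.
4. **What the recipient does.** The investigator registers adverse events, has database access except to the randomization module (Data monitoring section) and shares the analysis.
5. **What protection is stated.** For participants: no remote control and a non-rechargeable generator. For the investigator: a closed randomization module. The article describes no screening of what participants may report to the investigator.

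Steps 1 and 2 pull against each other, and steps 3 and 4 show why this matters.

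**How often it might happen.** The protocol gives no rate and expects very few adjustments. As an illustration only, let r be the assumed probability that a burst participant reports a sensation to the investigator, independently across the 20 burst participants (Sample size section). The chance of at least one report is 1 − (1 − r)^20, and the expected number is 20r.

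| Assumed r | At least one report | Expected reports |
|---|---|---|
| 2% | 1 − 0.98^20 = 33% | 0.4 |
| 5% | 1 − 0.95^20 = 64% | 1 |
| 10% | 1 − 0.90^20 = 88% | 2 |

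Over this range at least one disclosure is quite possible, but the expected number is at most two.

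**The case against.** A reader might infer that participants who feel stimulation are instructed to call the investigator, that any call reveals the arm, and that assessor blinding is therefore broken. The documents do not support this.

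- **Routing.** Participants may contact the investigator; they are not told to. The sentence on sensation names unblinded personnel for the adjustment. The investigator-first order is explicit only for a suspected ONS problem, which is broader than felt stimulation.
- **Content.** Discomfort at the generator or lead trouble can arise in either arm. A placebo participant may also believe that something is felt, or may make contact because nothing is felt. Only a described sensation points to burst, and it makes burst likely rather than certain.
- **Efficacy data.** Attack counts and questionnaires are entered electronically by participants, with automatic reminders for late entries. They depend on the participant's blinding, which this route leaves untouched.
- **Analysis.** It starts only after all follow-up, a blinded statistician takes part, and the primary analysis is by intention to treat.
- **Source.** The text is a condensed article, and call-handling instructions may sit in the full protocol or a trial manual.

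The first four points stand and set the limits of the finding. The last does not remove it: the point rests on a contact route that the article itself states in two sections and that works against its own separation rule, not on a missing procedure.

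**Conclusion.** The point holds as an avoidable weakness in the blinding procedure. The stated contact route can disclose likely burst allocation to the blinded person who registers adverse events and shares the analysis, contrary to the arrangement that unblinded staff deal with device events.

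Its size cannot be derived from the documents. The percentages above rest on assumed rates and on independence between participants, and they count reports, not certain unblindings. The exposure lies mainly in registering and attributing adverse events, which matters because safety is a primary endpoint, and secondarily in analysis decisions. The self-entered attack frequency is little exposed. The route should be changed, but it does not by itself invalidate the burst versus placebo comparison.

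**What to change.** Amend the Randomization and blinding and Adverse events sections together:

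1. Device-related contact in the blinded phase goes directly to the unblinded project nurse or programmer who would see the participant anyway.
2. Add a narrow exception to the rule that keeps unblinded staff out of data collection. They record stimulation sensations and setting changes in a restricted log, closed to the investigator and the statistician. The log is merged into the safety data after unblinding, so that no side effect is lost from the safety record.
3. All other adverse events go to the blinded investigator as now.
4. Any disclosure of likely allocation to the investigator, past or future, is logged with its date.

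Participants should not be told to keep sensations from blinded staff. Such an instruction would signal that a sensation reveals the arm and could weaken the participant blinding on which the efficacy outcomes depend.

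The cost is small: a changed contact point, first calls taken by the programming staff, and one restricted log. The documents do not say whether those staff are available for direct calls, so this needs to be confirmed.

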## Methods: data collection, management, and analysis

### Data collection and management

The study data is collected in compliance with the General Data Protection Regulation (GDPR). The paper consent forms are stored in a locked container. All other forms and questionnaires are electronic and are collected in the Research Electronic Data Capture (REDCap) database system hosted at Aarhus University [36, 37] in a dedicated project database.

Acquisition, storage, and analysis of the data are authorized by the Central Denmark Region (permit number 1–16-02–577-20).

### Statistical analysis

Statistical analysis will be conducted by the principal investigator and a statistician blinded for treatment allocation only after follow-up for all participants is completed. No interim analysis will be performed.

Characteristics of the patients will be presented using descriptive statistics to assess if balanced groups were obtained after randomization. The primary analysis will be conducted according to the intention-to-treat principle to avoid introducing bias. In a secondary analysis, a per-protocol analysis will be performed.

The primary outcome is a 30% reduction in attack frequency with TENS and ONS treatment compared to baseline. Relative change in attack frequency (in percent) will be analyzed using the Wilcoxon signed-rank test for paired variables, comparing the baseline data with data from the TENS trial and the trial with burst and tonic ONS, respectively. Because the changes in attack frequency are expectedly skewed [23], a non-parametric test will be applied. In cases with a minimum 30% reduction in attack frequency, sub-analyses will be made to group the treatment responders after relevant cutoffs.

Analysis of the secondary outcomes will be conducted according to the same principle, comparing data from each of the trial phases to baseline using a parametric or non-parametric test for paired variables, depending on the data distribution.

The feasibility of TENS as a predictor for ONS outcome will be evaluated by determining the sensitivity and specificity and calculating the predictive values.

Statistical data analysis will be performed using Stata 17.0 (StataCorp, College Station, USA-TX).

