**Methods:**

An investigator-initiated, double-blinded, randomized, placebo-controlled trial is conducted, including 40 patients with CCH. Eligible patients complete a trial with the following elements: I) four weeks of baseline observation, II) 12 weeks of transcutaneous electrical nerve stimulation (TENS) of the occipital nerves, III) implantation of a full ONS system followed by 2 week grace period, IV) 12 weeks of blinded trial with 1:1 randomization to either placebo (deactivated ONS system) or burst (paresthesia-free) stimulation, and V) 12 weeks of tonic stimulation.

The primary outcomes are the reduction in headache attack frequency with TENS and ONS and treatment safety. Secondary outcomes are treatment efficacy of burst versus tonic ONS, the feasibility of TENS as a predictor for ONS outcome, reduction in headache pain intensity (numeric rating scale), reduction in background headache, the patient’s impression of change (PGIC), health-related quality of life (EuroQoL-5D), self-reported sleep quality, and symptoms of anxiety and depression (Hospital Anxiety and Depression Scale, HADS).

Data on headache attack characteristics are registered weekly. Data on patient-reported outcomes are assessed after each trial phase.

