**Fig. 2 Fig2:**
[figure not shown]
Outcome parameters in correlation to trial phases and study visits. TENS, transcutaneous electrical nerve stimulation. ONS, occipital nerve stimulation. PGIC, patient's global impression of change. HADS, hospital anxiety and depression scale. EuroQoL-5D, European Quality of Life – 5 Dimensions

All questionnaires are electronic and are entered via a personal link sent automatically by e-mail. If the headache registrations and questionnaires are not completed within 24 h, an e-mail reminder is generated.

The data collected during each trial phase will be compared to the baseline and analyzed in order to evaluate the study endpoints listed in Table 4.

**Table 4 Tab4:** Study endpoints

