### Sample size

Based on our previous experience with ONS treatment [26], we estimate that 50% of the participants who receive active treatment with burst ONS will reach the primary endpoint of a 30% reduction in attack frequency. A blinded trial with burst ONS and placebo has to our knowledge not been carried out earlier, but we hypothesize that no more than 10% in the placebo group will meet the primary endpoint [35]. The sample size is calculated using Fisher’s Exact test based on the above-mentioned assumptions and with 80% power (two-tailed) and a α = 0.05, a total of 40 participants (20 in each allocation group) are needed to be enrolled in the study and an ONS-system implanted.

Each enrolled participant contributes their data regardless of whether they complete the project or not. In case of participants excluded after enrollment, the reason for exclusion will be described.

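### The ONS effect is tested within patients against a pre-TENS baseline; a randomised burst-versus-placebo comparison of attack frequency, adjusted for baseline and TENS-phase rates, should be stated instead

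*Protocol article*

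**What the plan says.** Study design fixes the order of events: "After an initial baseline period, all participants are treated with TENS". Implantation follows, then a 14-day grace period, and only then 1:1 randomisation to burst ONS or a device left off. The Abstract gives four weeks for baseline, 12 for TENS and 12 for the blinded phase, and adds: "Data on headache attack characteristics are registered weekly".

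Every phase has the same reference. Outcome measures states: "The data collected during each trial phase will be compared to the baseline". Statistical analysis repeats it for the primary endpoint: "The primary outcome is a 30% reduction in attack frequency with TENS and ONS treatment compared to baseline". The named test is a Wilcoxon signed-rank test of relative change, pairing baseline with the TENS phase and with burst and tonic ONS in turn. Secondary outcomes follow the same principle. TENS-phase counts have two stated uses: their own comparison with baseline, and the analysis of TENS as a predictor of ONS outcome.

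Sample size rests on a different contrast. It assumes that "50% of the participants who receive active treatment with burst ONS will reach the primary endpoint" and that "no more than 10% in the placebo group will meet the primary endpoint", and arrives at 20 per arm.

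**The concern.** The trial is sized on burst versus placebo, yet the stated efficacy test compares patients with their own past. By the start of the blinded phase a patient's attack rate may have moved because of TENS, surgery, time, or regression to the mean after entry at 15 or more attacks per month. A signed-rank test in the burst arm credits all of that to burst. In the placebo arm the same movement can produce a 30% reduction with the device off.

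The second issue is efficiency. Up to 12 weekly counts per patient lie between baseline and randomisation. They are valid covariates for a randomised comparison, even though TENS may have altered them, because they precede allocation. The stated test cannot use them. With 40 patients undergoing surgery, precision that is already paid for should not be left unused.

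**Working it through.** **Age of the baseline.** 12 weeks of TENS + 2 weeks of grace period = 14 weeks from the end of baseline to the start of the blinded phase, plus any wait for surgery.

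**The plan's own power figure.** The inputs are 50% v 10%, 20 per arm, "with 80% power (two-tailed) and a α = 0.05", and Fisher's "Exact test based on the above-mentioned assumptions".
- Uncorrected normal formula: n = [1.96·√(2·0.3·0.7) + 0.842·√(0.25 + 0.09)]² / 0.4² = (1.270 + 0.491)² / 0.16 = 19.4, so 20 per arm. This gives the stated 40.
- Exact two-sided Fisher power by enumeration: 74.2% at 20 per arm and 81.1% at 23. The named test therefore needs 46 patients for 80%. That is a separate matter, but it shows there is no slack.
- If placebo responders exceed 10%, Fisher power at 20 per arm falls to 57% (50% v 15%) and 41% (50% v 20%).

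**What a between-arm adjusted analysis could gain.** The documents give no SD and no correlation between phases, so all of the following rests on assumed values.

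*(a) Simulation, set A.* 20 per arm; weekly rate about 7; between-patient log-SD 0.5; TENS log effect −0.1 (SD 0.2); burst log effect −0.4 (SD 0.3), a cut of about one third; 1,500 trials per setting. ANCOVA is of log attack rate.

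| Phase log-SD, autocorrelation | Fisher, 30% responders | ANCOVA, baseline | ANCOVA, baseline + TENS |
|---|---|---|---|
| 0.2, 0 | 63% | 87% | 91% |
| 0.3, 0 | 39% | 71% | 76% |
| 0.3, 0.5 | 47% | 76% | 85% |
| 0.4, 0.5 | 31% | 60% | 72% |

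- Continuous baseline-adjusted analysis over Fisher: 87−63 = 24, 71−39 = 32, 76−47 = 29, 60−31 = 29 points.
- TENS covariate on top: 91−87 = 4, 76−71 = 5, 85−76 = 9, 72−60 = 12 points.
- Type I error was 4.8–5.9%. Reruns agreed to within about 3 points.
- With the SD of individual TENS response raised to 0.5, the TENS gain fell to about 1–4 points.
- These inputs imply about 14–28% placebo responders, above the protocol's 10%.

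*(b) Simulation, set B, calibrated to 50% v 10% responders.* 4,000 trials per setting.

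| Burst response | TENS response | Fisher | ANCOVA, baseline | + TENS |
|---|---|---|---|---|
| uniform | uniform or varied (log-SD 0.3) | 74–76% | about 98% | 99–100% |
| varied (log-SD 0.4) | uniform | 74% | 78–79% | 84–89% |
| varied (log-SD 0.4) | varied (log-SD 0.3) | 74–76% | 78–80% | 80–82% |

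Row by row, the step from Fisher to baseline ANCOVA is 23–24 points if burst acts uniformly and 3–5 points if it varies between patients. The TENS covariate adds 1–2 points in the uniform case. In the varied case it adds 6–10 points if TENS response is uniform and 1–4 if it varies. Part of any gap to Fisher is Fisher's conservatism: the normal test has 81% at the same inputs.

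*(c) Correlation grid.* With b baseline, t TENS phase and o outcome, R² = (r_bo² + r_to² − 2·r_bo·r_to·r_bt)/(1 − r_bt²). The residual variance ratio from adding t is (1 − R²)/(1 − r_bo²).
- Example: r_bo = 0.5, r_bt = r_to = 0.7. R² = (0.25 + 0.49 − 0.49)/0.51 = 0.490, and the ratio is 0.510/0.75 = 0.68. Power of 74% becomes 88%.
- Example: r_bo = r_bt = 0.7, r_to = 0.5. The ratio is 1.00 and power stays at 74%.
- From 74%, r_to of 0.3 gives 74–80%, 0.5 gives 74–82%, and 0.7 gives 82–96%.

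**The case against.** The strongest reply is that covariate choice belongs in an SAP, which is not shown, and that the article is a condensation. This stands for a bare missing covariate. It does not answer the main point, because the article positively states a paired test, and that test neither compares the arms nor takes a covariate.

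Three stronger readings are tempting, and the documents do not support them.
- A reader might infer that TENS-phase adjustment would sharply raise power. The gain depends on an unstated correlation and on how much TENS response varies between patients. The trial itself asks whether TENS response predicts ONS outcome, so small variation cannot be presumed.
- A reader might infer that the plan ignores the TENS-phase counts. It does not: they have their own comparison and the predictor analysis. They are only absent from the estimate of the ONS effect.
- A reader might infer that the old baseline biases burst against placebo. Movement before randomisation falls on both arms, so it costs precision in a randomised contrast without biasing it. The bias lies in the uncontrolled within-patient comparison. TENS carry-over is possible but not documented, and the four weeks before any trial treatment are a defensible reference for defining a responder.

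It is also fair that Fisher's test is named only for the sample size and that set A has a higher placebo rate than the protocol assumes. The 31–63% in set A is therefore not the power of the plan.

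**Conclusion.** The concern holds for the stated test. A signed-rank test against a baseline at least 14 weeks old cannot isolate the effect of burst, and it leaves pre-randomisation data unused in estimating that effect. This follows from the text alone.

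The size of the power gain is conditional. In set A most of it comes from comparing attack frequency between arms as a continuous, baseline-adjusted measure. In set B that is so only if burst acts fairly uniformly. The TENS covariate is a useful addition of 1 to about 12 points across the two simulations, and near zero in parts of the correlation grid. The simulations used log-rate ANCOVA, so they indicate rather than give the power of a negative-binomial model. The change should be made, as a low-cost improvement whose gain is likely but cannot be quantified from the documents.

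**What to change.** State as the efficacy analysis of the blinded phase, by intention to treat, a burst-versus-placebo comparison of attack frequency:
- Use negative-binomial regression on the weekly counts, which accommodates zero counts. Either total them per patient with log weeks recorded as offset, or allow for repeated weeks within a patient.
- Adjust for log baseline rate and, as a pre-specified further covariate, log TENS-phase rate. Set a rule in advance for a covariate rate of zero.
- Report the adjusted rate ratio with its 95% CI beside the between-arm 30% responder comparison. The responder stays defined against the original baseline.
- Keep the paired tests for TENS and tonic ONS, described as uncontrolled before-after comparisons.

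The cost is analysis wording before unblinding. Analysis is planned only after all follow-up, with no interim look, and the counts are already collected, so there is no patient burden. The downside is slightly more modelling and one or two extra parameters with 40 patients.

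### The primary endpoint is a 30% reduction in attack frequency, but the only analysis named for it is a signed-rank test whose null is zero change

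*Protocol article*

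**What the plan says.** Table 4 of the protocol article lists the first primary endpoint as "30% reduction in attack frequency with TENS and ONS". The Statistical analysis section repeats it: "The primary outcome is a 30% reduction in attack frequency with TENS and ONS treatment compared to baseline".

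The Sample size section uses the same endpoint as a per-participant event. It expects that "50% of the participants who receive active treatment with burst ONS will reach the primary endpoint of a 30% reduction in attack frequency" and that "no more than 10% in the placebo group will meet the primary endpoint". It adds: "The sample size is calculated using Fisher’s Exact test", which is a method for comparing proportions.

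The only test named for the primary outcome is in the Statistical analysis section: "Relative change in attack frequency (in percent) will be analyzed using the Wilcoxon signed-rank test for paired variables, comparing the baseline data with data". The data set against baseline are those "from the TENS trial and the trial with burst and tonic ONS, respectively". No shift of −30%, responder proportion or target is attached to it. The 30% comes back one step later, as a filter: "In cases with a minimum 30% reduction in attack frequency, sub-analyses will be made to group the treatment responders after relevant cutoffs".

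**The concern.** The endpoint and its analysis answer different questions. The endpoint asks whether attack frequency fell by 30%, and in the Sample size section how many participants achieved that. The signed-rank test asks whether the paired changes are centred on zero. A modest fall shared by everyone, or a large fall in a minority, can give a small p-value without answering the endpoint's question.

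This matters most for TENS and tonic ONS. By the Study design section, all participants receive both, with no concurrent comparator. The 30% threshold is then the only stated guard against reading a small drift from baseline as a treatment success, and the named test does not apply it. The same holds for burst ONS (n=20) when it is compared with its own baseline.

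**Working it through.** **1. The plan's own figure.** Inputs from the Sample size section: 50% versus 10%, two-tailed α = 0.05, power 80%, 20 per arm. The uncorrected two-proportion formula is

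n = [1.960·√(2·0.30·0.70) + 0.842·√(0.50·0.50 + 0.10·0.90)]² / (0.50 − 0.10)² = (1.270 + 0.491)² / 0.16 ≈ 19.4, so 20 per arm and 40 in total.

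The stated 40 follows from that formula. Two-sided Fisher's exact test at 20 per arm has power 0.742 and first passes 80% at 23 per arm (0.811), which is a separate matter. What counts here is that the inputs are proportions of participants reaching 30%, so the plan itself reads the endpoint as a responder event.

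**2. What the named test uses.** For participant i let dᵢ = 100 × (phase frequency − baseline frequency) / baseline frequency. The signed-rank statistic is W = Σ sign(dᵢ)·rank(|dᵢ|), referred to a distribution symmetric about dᵢ = 0. The value −30 does not enter W or its reference distribution, whatever the spread.

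**3. How often it is significant below 30%.** The article gives no variance, so these figures illustrate the point under assumptions. Model: weekly attack rates lognormal with median 7, log-SD 0.5 and floor 3.5 per week (about 15 per month); weekly counts Poisson with gamma week-to-week variation of variance 0.1, 0.3 or 0.5 (low, medium, high); 4 weeks of baseline and a 12-week phase as in the protocol; two-sided signed-rank test at 0.05, counted when the median change is negative. Repeat runs differ by a few points.

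| True effect | n | Significant: low / medium / high |
|---|---|---|
| Uniform 15% fall | 40 | 0.69 / 0.27 / 0.14 |
| Uniform 20% fall | 40 | 0.94–0.96 / 0.58–0.64 / 0.33–0.35 |
| Uniform 25% fall | 40 | >0.99 / 0.86–0.87 / 0.59–0.62 |
| Uniform 20% fall | 20 | 0.67–0.69 / 0.33–0.34 / 0.18–0.19 |
| 40% fall by 60%, rest unchanged | 40 | 0.81–0.82 / 0.60–0.61 / about 0.41 |

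At the uniform 20% fall with n=40, about 31–36% of participants show an observed reduction of at least 30%. In the last row the share is about 44–45%, with a median change of about −22% to −24%.

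**4. Sensitivity to the assumed spread.** For a 20% reduction with n=40:
- Normally distributed changes, SD 20/30/40 points: significant in 1.00/0.98/0.85, with 31/37/40% of participants at or beyond 30%.
- Right-skewed lognormal changes, log-SD 0.3/0.5/0.7: 0.98/0.50/0.18, with 33/39/42% at or beyond 30%.

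The rate varies widely. The absence of the threshold from the test does not.

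**5. Precision of a direct read-out.** Exact (Clopper–Pearson) 95% limits for x of n are the 2.5% quantile of Beta(x, n−x+1) and the 97.5% quantile of Beta(x+1, n−x):
- 10 of 20: 0.272 to 0.728.
- 20 of 40: 0.338 to 0.662.

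**The case against.** The strongest reply is that the article never says p<0.05 means the 30% endpoint was met. A reader might infer that a significant signed-rank result is the formal criterion for primary success, but no decision rule is written down. The section can be read as a test of change followed by responder reporting, and the choice of deciding result might sit in an analysis plan that is not shown. That stands against any claim that the protocol would declare success falsely. It does not remove the mismatch. The article does name an analysis for the primary outcome, and that analysis does not address it. The responder step that follows only subdivides participants who have already passed 30%.

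A reader might also take the rates above as inflated type I error. They are not. Attack frequency truly falls in every scenario shown, so the zero-change null is false and the rates are power. With no change, the count model declares a reduction in under 1% of trials at n=40. Nor can one say that the endpoint is false in these scenarios: on the responder reading, no target proportion is stated for TENS or tonic ONS, and 44–45% observed responders is not far from the 50% assumed for burst.

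Finally, the sample size rests on a burst-versus-placebo responder comparison that the Statistical analysis section does not name. That is a separate and weightier point. Adding such a test would mend the blinded phase but leave TENS and tonic ONS tested only against zero.

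**Conclusion.** The point holds in a limited form. The primary efficacy endpoint is a 30% reduction, used as a per-participant response in the Sample size section. The one analysis named for it can establish only that attack frequency changed. That conclusion rests on the text and on how the test is built, not on any assumed spread.

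The size of the risk does depend on assumptions the article does not supply. For a uniform 20% reduction in 40 participants, significance ranges from about 33% to 96% in the count model, and from 18% to nearly 100% across the other spreads tried. The documents support a finding of likely over-interpretation. They do not support a finding of a written false-success rule or of a test that exceeds its nominal error rate. The analysis text should be changed before the data are analysed.

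**What to change.** In the Statistical analysis section:
- For each phase (TENS, blinded phase by arm, tonic ONS), make the primary read-out the proportion of participants with at least a 30% reduction from baseline, with an exact 95% confidence interval.
- Report the median percent change with its 95% confidence interval beside it.
- Keep the signed-rank test as supportive, and state that its significance alone does not mean the primary endpoint was met.

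I would not go further and require the confidence limit for the median to lie beyond −30%. In the count model, with 50% true responders falling by 60% and n=40, testing the change against −30% succeeds in only about 0–2% of trials. A treatment performing at the responder rate the plan hopes for would almost always fail.

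The cost is a few sentences, with no new data or participants. Analysis is planned only after all follow-up is complete, so the change can still be made in advance of it. The downsides are wide intervals (27–73% with n=20 and 34–66% with n=40 at 50% responders) and a less favourable headline. The proportion is also not proof of effect in an uncontrolled phase: with no average change and normal spread of SD 20/30/40 points, 7/16/23% of participants would still reach 30%.
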